## Abstract

**Introduction**: Poor outcomes following IVF treatments are speculated to be due to the transfer of aneuploid embryos that cannot be identified based on morphological evaluation alone. This leads to patients requiring numerous embryo transfers and, consequently, a prolonged time interval before live birth. Embryo selection following preimplantation genetic testing for aneuploidy (PGT-A) with next-generation sequencing (NGS) has been suggested as an intervention to shorten time to pregnancy in women undergoing in vitro fertilisation (IVF). Past studies assessing the clinical efficacy of PGT-A in improving clinical outcomes have been conflicting and the associated clinical pregnancy rates and live birth rates following the transfer of a mosaic embryos have yet to be determined. None of the existing studies solely included women of advanced reproductive age (ARA). The pilot study and proposed RCT will determine if, compared to morphological evaluation alone, the use of PGT-A through NGS is a more clinically effective, safer, and more cost-effective way to provide IVF treatment in women of advanced reproductive age. **Method and Analysis**: The proposed pilot study will aim to randomise 100 patients within a single-centre study to evaluate recruitment, randomisation, and adherence to study protocol and allocated trail arms by participating patients. The results of the pilot study will enable us to determine the sample size for a larger study to establish the effectiveness of PGT-A in ARA women. **Ethics and Dissemination**: The study (Integrated Research Application System Number 236067) received approval from the Health Research Authority and Health and Care Research Wales (HCRW) and the East Midlands—Leicester South Research Ethics Committee (20/EM/0290). The results will be made available to patients, the funders, the Reproductive Medicine societies, and other researchers. **Trial registration**: ClinicalTrials.gov Identifier: NCT05009745, n.

## 1. Introduction

### 1.1. Background

The selection of the most viable embryo is typically based solely on light microscopy and morphological assessment in assisted reproductive technologies (ART) [1,2,3]. However, despite significant technological and scientific advances in the field, many women still fail to achieve clinical pregnancy or live birth, despite the transfer of embryos classified as good quality by various guidelines [4,5,6,7,8]. This high rate of failure is believed to due to the limitations of relying solely on morphological evaluation, which is an inefficient method of determining embryo ploidy, unable to accurately distinguish between euploid, aneuploid, or mosaic embryos, which have distinct implantation potentials [3,7,8]. The human embryo aneuploidy rate is reported to range between 30% and 50% when under 35 years of age and to increase to 80% in patients aged 42 years of age or older [9,10], reflecting the higher miscarriage rates and lower live birth rates often seen in women of advanced reproductive age. Often, to increase the chances of a live birth, assisted-conception units rely on the transfer of multiple embryos graded as good on morphological criteria alone. However, multiple-embryo transfer is known to increase the risk of multiple pregnancies, which are associated with significant foetal, maternal, and neonatal risks, as well as long-term complications [11]. In view of this, providing patients with an added level of single-embryo selection beyond a static or dynamic morphologic evaluation is of increasing clinical importance.

Preimplantation genetic testing for aneuploidies (PGT-A), combined with next-generation sequencing (NGS), aims to identify and transfer euploid embryos with the highest implantation potential, while excluding aneuploid embryos that are likely to arrest in development and lead to negative pregnancy outcomes [12,13,14]. In additional to shortening the time-to-pregnancy timeline, reducing the miscarriage rate, and improving live birth rates, IVF with PGT-A also aims to promote single-embryo transfer, thereby reducing the risk of multiple births without lowering overall IVF success rates [13,15].

However, with the evolution of PGT-A techniques from fluorescence in situ hybridization (FISH), which only analysed up to eight chromosomes, to NGS, which provides a complete analysis of all 23 chromosomes [16], a limited number of clinically relevant randomised controlled trials are available, and the use of PGT-A, and particularly whether it truly improves live birth rates, remains contentious [17,18]. Earlier studies on FISH are now considered outdated and cannot be applied to current practice [9,19,20]. Another concern with past technology was the inherent risk of inaccuracies due to signal, which increases the rate of false negatives and false positives. Past technology also lacked the ability to define, detect, and differentiate between embryos with low and high mosaic genetic constitutions, a common finding in IVF-derived human embryos [21].

### 1.2. Current Evidence

Currently, few trials exist assessing the clinical benefit of IVF with PGT-A via NGS vs. IVF with no PGT-A, and a meta-analysis of their findings were inconclusive. Challengers of PGT-A dismiss earlier trials due to concerns over the ‘intention-to-treat’ criteria, focusing instead on the ESTEEM and STAR trials, which indicated that PGT-A is effective in increasing pregnancy rates [19,22]. However, supporters of PGT-A argue that these trials, along with all RCTs conducted so far, demonstrate at least some positive outcomes for PGT-A, arguing that participants in the STAR trial had an average age of 28 years old, which is associated with a low aneuploid rate. However, post hoc analysis in women aged 35–40 suggested a notable increase in OPR per embryo transfer for PGT-A cycles [19]. Challengers argue that this approach is not valid, despite the results of both the STAR trial and the SART study, which compiled data from U.S. IVF clinics, both showing statistically significant differences in the over-35 age category [19,23]. These findings were described as contentious and not deemed reliable by the HFEA’s Scientific and Clinical Advances Advisory Committee (SCAAC). Other studies have faced significant methodological criticisms, suggesting they contained underpowered study designs, selection bias, inadequate blinding, and a lack of multi-centre validation.

Superficially, even the latest multicentre study detailing clinical outcomes from 1212 patients did not identify IVF without PGT-A as being associated with superior outcomes compared to PGT-A [24]. However, this study has been criticised for its flaws—it had an average participant age of 29 years old, a euploidy rate of 69.8%, and the methodology used appear to be biassed against PGT-A, with the use of cumulative live birth rate as a primary outcome [23], which may not accurately reflect PGT-A’s superiority due to these biases and differences in embryo selection and transfer practices. The authors also only selected three top-quality embryos, based on morphology, for biopsy and did not perform a biopsy on all available embryos, which is routine clinical practice. The study also did not account for the transfer of low-grade mosaic embryos, which can be performed in real life clinical care [24]. Therefore, the clinical effectiveness of PGT-A as a selection tool in women with an expected high aneuploidy rate, namely those above the age of 35 years, remains to be determined.

Our study’s novelty lies in its focus on an older age group, where the prevalence of aneuploidy and mosaicism is higher, and evaluation of the impact of advanced PGT-A methods on live birth rates. Additionally, we will specifically address the outcome of mosaic embryos—a critical aspect that was often overlooked in previous studies. By examining how mosaic embryos affect clinical outcomes and incorporating them into the analysis, our study will provide valuable insights into the practical implications of the use of PGT-A for diverse embryo classifications.

By addressing these aspects, we aim to offer new evidence on the effectiveness of PGT-A in improving IVF outcomes, particularly for older women and in the context of mosaic embryo management.

## 2. Support for This Study

The need for a robust RCT assessing the potential clinical benefit of PGT-A in women of advanced reproductive age is recognised by the European Society of Human Reproduction (ESHRE), which has also recognised that the cumulative live birth rate (CLBR) may not effectively demonstrate PGT-A’s superiority due to selection bias, the exclusion of potentially viable embryos, and differences in multiple transfer opportunities [25].

With advancements in embryo genetic screening, there is now a reinvigorated interest in the use of the new PGT-A with NGS in IVF to reduce miscarriage rates and time to pregnancy, especially in women of advanced reproductive age; this is listed as a research recommendation by the European Society of Human Reproduction [21,25].

In the context of this pilot study, our design will facilitate the evaluation of embryo ranking based on implantation potential, including the assessment of mosaic embryos. However, given the exploratory nature of the pilot, our findings will be preliminary and focused on feasibility. We aim to gather initial data that will inform future studies, rather than to draw definitive conclusions about clinical pregnancy rates at this stage.

### 2.1. Objective

In the proposed pilot study, we will evaluate recruitment, randomisation, and adherence to study protocol and allocated trail arms by participating women. We aim to incorporate the results of the pilot study into the main RCT, for which ethical approval will be sought. Participating women will be informed of our intention to include the pilot data in the full study.

The purpose of the RCT will be to determine if a policy of embryo selection and transfer based on morphological evaluation and PGT-A with NGS is a more clinically effective, safer, more cost-effective, and acceptable way to provide IVF treatment in women of advanced reproductive age compared to the routine practice of embryo selection and transfer based on morphological evaluation alone.

### 2.2. Trial Design

The study will be a prospective, allocation concealed, two-arm, parallel RCT. Trained research personnel will recruit eligible patients from within the assisted-conception clinic and obtain informed consent using the agreed consent form.

### 2.3. Study Setting and Timeline

The pilot phase of the study, to be conducted at King’s Fertility within King’s College Hospital NHS Foundation Trust, will provide an estimate of the recruitment rate, randomisation rate, and adherence to the study.

### 2.4. Inclusion Criteria

Any women aged 35–42 years undergoing IVF ± ICSI treatment for infertility, with the aim of a fresh embryo transfer, will be eligible to participate in the study.

The trial population was chosen to be consistent with expert (national and international) consensus opinion and a UK-based survey of fertility specialists which suggested that women of advanced reproductive age (35 years and above) undergoing IVF are most likely to benefit from PGT-A.

### 2.5. Exclusion Criteria

Patients undergoing preimplantation genetic testing for inherited genetic disorders;Gamete donation cycles;Patients with untreated hydro-salpinges;Patients with untreated uterine pathology (e.g., endometrial polyps, submucous fibroids, intramural fibroids > 5 centimetres in maximum diameter, intrauterine adhesions, uterine septa);Patients currently participating in research involving interventions or who were recently (within a month) involved in interventional research.

### 2.6. Consent

Women aged between 35 years and 42 years old who meet the inclusion and exclusion criteria and who wish to undertake an IVF/ICSI treatment cycle will be invited to participate in the trial. Recruitment will continue through monitoring scans up to the day of egg collection, and eligible women and patients will be given a participant information sheet about the trial. If a woman and her partner agree to participate in the trial, a formal signed trial consent) will be obtained from both partners, conducted in accordance with ethical standards.

### 2.7. Randomisation

#### Software

Third party, distant, internet-based block randomisation with minimisation will be used to ensure randomisation and complete allocation concealment. Women will be randomised into the trial using a secure online randomisation system, accessible via the MedSciNet Clinical Trial Framework (www.medscinet.net). This system will be available 24/7, with a toll-free telephone randomisation service available from Monday to Friday, 09:00 to 17:00 UK time, excluding bank holidays and university closure days. This option will provide flexibility for researchers needing assistance.

Before randomisation, investigators will complete registration paperwork to collate necessary participant information. All required data must be submitted; if any information is missing, randomisation will be paused until it is provided. Upon verification of eligibility and baseline data, the trial number and treatment pack number will be assigned.

### 2.8. Minimisation Algorithm

The randomisation system (allocation ratio 1:1) will employ a minimisation algorithm to ensure balance across the following factors: IVF clinic, female age (35–37, 38–39 and 40–42 years), BMI (20–<25, 25–<30, ≥30), previous live birth, type of ovarian stimulation protocol (gonadotrophin-releasing hormone (GnRH) agonist or GnRH antagonist; human chorionic gonadotrophin (hCG) or GnRH agonist trigger), and standard IVF or ICSI.

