## 6. Study Design

### 6.1. Intervention Regimens

The study design describes a single-centre, randomised, placebo-controlled, two-arm study (see Figure 1). The experimental (intervention) strategy will be to perform PGT-A via NGS on good-quality embryos at the fully expanded blastocyst stage.

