### 6.2. Timing of Randomisation

Randomisation will occur on day 3 following egg collection. At this point, all consented patients will be evaluated for eligibility. Specifically, patients will be randomised if they have at least three good-quality embryos, as assessed using the embryo-scoring system of the Association of Clinical Embryologists (UK).

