### 6.8. Statistical Analysis

As this is a pilot study, the main emphasis will be on the acceptability of the intervention and the randomisation process to couples, and on adherence to the protocol. However, following the “All Trials” principle, we will also present a full analysis appropriate for a randomised controlled trial [27].

Baseline comparisons will be made of female age, previous live birth, cause of infertility, number of previous IVF attempts by the woman, ovarian reserve (assessed by the total antral follicle count: 7 or less; 8–20; more than 20), type of ovarian stimulation protocol (gonadotrophin releasing hormone (GnRH) agonist or GnRH antagonist; human chorionic gonadotrophin (hCG) or GnRH agonist trigger), and standard IVF or ICSI. The results will be presented as percentages or mean (SD), as appropriate.

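### The day-3 good-quality embryo count decides entry and is known before allocation, but it is not a minimisation factor: a modest loss of balance and precision in the secondary clinical outcomes

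*Protocol article*

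**What the plan says.** All references are to the protocol article.

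- **Timing and entry (6.2).** "Randomisation will occur on day 3 following egg collection", and "patients will be randomised if they have at least three good-quality embryos". There is a lower limit and no upper limit.
- **Order of steps (2.7, Software).** "Upon verification of eligibility and baseline data, the trial number and treatment pack number will be assigned". Whatever decides eligibility is therefore on record before the arm is assigned.
- **Minimisation (2.8).** Allocation, at 1:1, uses a "minimisation algorithm to ensure balance across the following factors: IVF clinic, female age (35–37, 38–39 and 40–42 years), BMI" in three bands, then "previous live birth, type of ovarian stimulation protocol" and trigger, and IVF or ICSI. No measure of embryo number appears.
- **Baseline list (6.8).** "Baseline comparisons will be made of female age, previous live birth, cause of infertility, number of previous IVF attempts by the woman, ovarian reserve" by antral follicle count, plus stimulation protocol and trigger, and IVF or ICSI. Embryo count is not listed here either.
- **Centres.** The Abstract and sections 2.3 and 6.1 describe a single-centre pilot. Section 6.7 mentions further centres only for the full study.
- **Use of the data (2.1, 4, 5).** The primary endpoint is feasibility. The secondary endpoints include clinical pregnancy per randomised woman and time to a pregnancy ending in live birth. The pilot results are intended to be included in the main RCT.

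**The concern.** The protocol delays randomisation to day 3 so that embryos can be graded and counted, and then makes no use of the count beyond the threshold. A woman with three good-quality embryos and a woman with eight enter on the same footing. Embryo supply feeds into how many blastocysts exist, whether one is suitable for transfer, and how many transfers a woman can have. It is therefore likely to be prognostic for pregnancy per randomised woman and for time to pregnancy.

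At about 50 women per arm, the arms can differ in supply by chance. That adds noise to the clinical comparisons, and the noise travels with the pilot data into the main trial. Adjustment in the analysis can recover much of the precision, but balance itself can be obtained only at allocation. The choice of factors in section 2.8 is therefore worth raising now.

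**Working it through.** The article states no figure for expected balance, so there is none to reproduce. The check compares the lists and then sizes the effect under stated assumptions.

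**1. Lists side by side.** The count is fixed before allocation (6.2; 2.7), is absent from the explicit factor list (2.8), and is absent from the variables named in 6.8. Antral follicle count is in 6.8, but it is a more distant measure and is not a minimisation factor.

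**2. Chance imbalance with no balancing.** Take 100 women, 50 per arm, of whom K have a high count. The number X in one arm is hypergeometric (100, K, 50), and the arm difference is |X − (K − X)|/50.

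| Share with high count (assumed) | P(difference ≥ 10 points) | P(difference ≥ 20 points) |
|---|---|---|
| 50% | 0.317 | 0.071 |
| 30% | 0.275 | 0.049 |

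**3. Chance imbalance under minimisation.** Simulation of 3,000 trials of 100 women, using marginal totals. Assumed, and not in the article: assignment probability 0.8, the count split 50:50, and all factors independent.

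| Factors | P(≥ 10 points) | P(≥ 20 points) | Mean absolute difference, age 40–42 (points) |
|---|---|---|---|
| As listed, with clinic constant | 0.303 | 0.047 | 3.52 |
| Clinic dropped | 0.327 | 0.045 | 3.26 |
| Count added, clinic kept | 0.019 | 0.000 | 3.63 |
| Count added, clinic dropped | 0.014 | 0.000 | 3.50 |

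Adding the count nearly removes the imbalance at no material cost to balance on age. Keeping or dropping the constant clinic factor makes no material difference. If the count is related to age or stimulation protocol, the listed factors already balance part of it, and 0.303 is somewhat high.

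**4. Imbalance in the mean count.** If the count has an SD of 2.5 to 3 (assumed), the SE of the difference in means is SD × √(2/50) = 0.50 to 0.60. A difference of at least 0.75 embryo then has probability 0.134 (0.75/0.50 = 1.5 SE) to 0.211 (0.75/0.60 = 1.25 SE).

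**5. What embryo number does for one woman.** P(at least one euploid blastocyst) = 1 − (1 − b·e)ⁿ, with b the share of good day-3 embryos reaching blastocyst (assumed 0.5) and e the euploid share. Section 1.1 gives aneuploidy of 30–50% under 35 and 80% at 42 or older, so e is taken as 0.4 with a range of 0.2 to 0.5.

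| e | n = 3 | n = 5 | n = 8 |
|---|---|---|---|
| 0.2 | 0.271 | 0.410 | 0.570 |
| 0.4 | 0.488 | 0.672 | 0.832 |
| 0.5 | 0.578 | 0.763 | 0.900 |

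This treats embryos as independent and leaves out low-mosaic embryos, which section 6.4 also allows to be transferred, so it understates the chance of having something to transfer.

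**6. From imbalance to outcome.** At e = 0.4 the slope is (67.2 − 48.8)/2 = 9.2 points per embryo from 3 to 5, and (83.2 − 67.2)/3 = 5.3 from 5 to 8. An imbalance of 0.75 embryo shifts the chance of at least one euploid blastocyst by 0.75 × 5.3 = 4.0 to 0.75 × 9.2 = 6.9 points. At an assumed 50% pregnancy per transfer, that is about 2.0 to 3.5 points of pregnancy per woman. The sampling SE of an arm difference at an assumed 40% with 50 per arm is √(2 × 0.24/50) = 9.8 points. The shift is thus between a fifth and about a third of that SE.

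**The case against.** **Nothing in section 2.8 is wrong.** This stands. The factor list is legitimate and includes age, which section 1.1 ties to aneuploidy. Leaving out a prognostic factor does not bias a randomised comparison, and the confidence intervals promised in section 8 already allow for chance imbalance.

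**Clinic takes a place that the count should have.** A reader might infer this because clinic has one level in the pilot. The documents do not support it. Minimisation has no fixed number of places, and a constant factor only adds weight to overall arm-size balance. Its presence makes sense if pilot data are pooled with a multicentre stage (2.1, 6.7).

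**The baseline table would hide the imbalance.** This is also tempting and also not established. The list in 6.8 is visibly incomplete: BMI is missing from it although minimisation requires it. Section 6.5 says that all baseline characteristics are collected, and a full protocol or analysis plan may list more.

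**Adherence, part of the primary endpoint, is at risk.** Section 7.3 treats PGT-A women with no embryos to biopsy as deviations. That is a proportion within one arm. It depends on that arm's supply, and balance between arms barely protects it.

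**The pilot is about feasibility, and the effect is small.** Both are true. Sections 2 and 6.7 make the clinical results preliminary, and section 6.5 ends pilot follow-up at the test or scan after transfer, which limits the role of later transfers except for time to pregnancy. What remains is that the count is already needed for eligibility and is close to the outcome, and that a later analysis plan cannot restore balance at allocation.

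**Conclusion.** The point holds as an optional improvement. A variable that the protocol itself uses to decide entry, and that is known before allocation, is left out of the minimisation factors. Under the assumptions above, the listed factors leave about a 30% chance of a 10-point or larger arm difference in the share of women with a high count, and about 5% for 20 points. Including the count brings these to 1–2% and about zero.

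The effect on the clinical comparison is modest: about 2 to 3.5 points of pregnancy per woman for an imbalance that would arise by chance in some 13–21% of such pilots, against a sampling SE near 10 points. These sizes rest on assumed blastocyst, euploidy and pregnancy rates and an assumed SD, none of which the article gives. That the count is prognostic is itself inferred from its place in the treatment pathway.

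Neither bias nor a threat to the feasibility endpoint follows. The cost is in balance and precision for the secondary clinical outcomes and for the pilot data carried forward.

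**What to change.** 1. Add the day-3 good-quality embryo count to the factors in section 2.8 in bands, for example 3–4, 5–7, and 8 or more. Leave IVF clinic in the list: it is inert in the pilot and needed if centres are added.
2. Name the count as a prespecified covariate in the between-arm models of the clinical outcomes, and include it in the baseline summary in section 6.8.
3. If the randomisation system is already in use, make only the changes in item 2 now and add the factor for the main trial.

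Cost: one more minimisation factor, a configuration change, and possibly a protocol amendment, which section 7.4 would send to the ethics committee if substantial. The covariate and baseline changes need no new data, because the count is already assessed for eligibility. Women allocated before a change would not have been balanced on the count, and for them the covariate does the work.
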